## Abstract

**Introduction:**

Evidence on the impact of nutrient-rich animal source foods such as eggs for improving child growth and cognition is inconsistent. This study aims to examine the impact of an egg intervention in children, along with behaviour change communication (BCC) to the mother, on linear growth and cognition, and nutritional status in children aged 9–18 months.

**Methods and analysis:**

A 9-month open-labelled randomised controlled trial will be conducted in three urban slums in Hyderabad, India, as a substudy of an observational cohort study (n=350) following pregnant women and their children until 18 months of age in a population at risk of stunting. The children born to women enrolled during the third trimester of pregnancy will be block randomised in a 1:4 ratio into the intervention (n=70) and control (n=280) groups. Children in the intervention group will be supplemented with one egg per day starting from 9 months until 18 months of age. BCC designed to enhance adherence to the intervention will be used. The control group will be a part of the observational cohort and will not receive any intervention from the study team. The primary outcome will be length-for-age z-scores, and the secondary outcomes will include cognition, blood biomarkers of nutritional status including fatty acid profile and epigenetic signatures linked with linear growth and cognition. Multivariate intention-to-treat analyses will be conducted to assess the effect of the intervention.

**Ethics and dissemination:**

The study is approved by the Institutional ethics committees of ICMR-National Institute of Nutrition, Hyderabad, India and London School of Hygiene and Tropical Medicine, UK. The results will be published in peer-reviewed journals and disseminated to policy-makers. Findings will also be shared with study participants and community leaders.

**Trial registration number:**

CTRI/2021/11/038208

WHAT IS ALREADY KNOWN ON THIS TOPICPrevious studies using single or multiple micronutrients or cereal legume-based food supplements have shown only modest impact on child stunting.Evidence on the impact of nutrient dense animal source foods such as eggs for improving child growth and cognition is inconsistent.WHAT THIS STUDY ADDSComprehensive evidence on the impact of daily egg supplementation during 9–18 months of age on the linear growth, cognition, nutritional biomarkers and epigenetic outcomes.HOW THIS STUDY MIGHT AFFECT RESEARCH, PRACTICE OR POLICYEggs provide several critical nutrients to support the infant growth and development and egg supplementation is a promising option for nutrition programmes.Therefore, the trial has a potential for immediate scale-up.

## Introduction

The high prevalence of stunting in children under 5 years of age in India (35%) remains a cause of concern given the associated long-term negative consequences on cognition, physical work capacity, earning potential and risk of chronic diseases in adulthood.^1–4^ Childhood stunting is common among populations residing in adverse environments with limited access to nutrient-dense foods and poor sanitation.^5^ In these environments, children’s diets are predominantly cereal-based, with low amounts of animal source foods (ASFs) that contain high-quality complete protein, and do not meet the high nutrient needs of young children.^6^ Improving the quality of early childhood diets and reducing child stunting is therefore a public health priority in India.

Previous evidence based on randomised controlled trials (RCTs) evaluating supplementation with cereal legume-based complementary foods or single or multiple micronutrient interventions in children has shown a limited impact on linear growth.^7–9^ The emerging evidence suggests that locally available ASFs such as eggs could play an important role in improving linear growth of young children.^10^ However, the evidence is mixed, and the impact of an egg intervention on linear growth and stunting prevalence appears to vary in different settings depending on the dietary patterns and baseline prevalence of child stunting. For example, an RCT in 163 children (6–9 months) from Ecuador assessed the impact of egg supplementation (one egg per day for 6 months) and showed a reduction in the prevalence of stunting by 47% and underweight by 74% in the intervention arm (n=83).^11^ However, in a similar trial in 660 children (6–9 months) from Malawi, an egg intervention did not have a beneficial effect on linear growth, possibly due to low baseline prevalence of stunting and background diets being rich in ASFs.^12^ In another RCT from Malawi (9-month-old children, N=267), the addition of egg powder with bovine colostrum to complementary feeds resulted in lower prevalence of stunting in the intervention arm (n=135, RR=0.70; 95% CI=0.52 to 0.94).^13^ Interventions such as preventive small-quantity lipid-based nutrient supplements for children aged 6–23 months, have shown positive impact on child growth.^14^ Compared with such interventions, a locally available ASF such as egg will be cost-effective and scalable.^15^ The aetiology of stunting is complex and poorly understood and the effect of interventions may differ between countries and ethnicities. There is no evidence available from the Indian subcontinent, where the stunting prevalence is high, and the ASF intake is low.

Eggs provide several nutrients critical to infant growth and development which include all the essential amino acids making it a high-quality/complete protein, docosahexaenoic acid (DHA) and micronutrients such as vitamin B_12_ which are important for neural development and immune function.^10^ Eggs are among the richest sources of choline, which is necessary for the production of phospholipids, cell membrane integrity and the conversion of acetylcholine and sphingomyelin necessary for brain development and function.^16^ Dietary choline intake can modulate DNA methylation, therefore, egg supplementation may also impact the epigenetic signatures.^17^ Epigenetics is one of the candidate mechanisms linking early life factors to physical and cognitive development with consequences across the life course.^18–21^ Evaluation of epigenetics signatures linked with stunting is central to the Action Against Stunting Hub (AASH) observational cohort.^22^

In India, eggs are more affordable than other ASFs and are relatively simple to store and prepare. Egg supplementation is a promising option in government nutrition programmes. In recent years, a few states in India have included eggs in supplementary feeding programmes for pregnant women and children in the age group 7 months to 6 years.^23 24^ However, systematic impact evaluation of these interventions on anthropometric, biochemical or cognitive outcomes has not been done. We hypothesise that daily egg supplementation (accompanied by behaviour change communication (BCC) to increase compliance to the intervention) starting at 9 months will improve linear growth and reduce the incidence of stunting at 18 months of age.

The proposed Eggs for Improving Nutrition, cognitive development and reducing linear growth retardation among Infants and young Children (ENRICH) study aims to evaluate the effect of daily supplementation with an egg in children from 9 months to 18 months of age (accompanied by behaviour change advice to the mother to increase compliance with the intervention) on:

Linear growth and stunting at 18 months.Cognition, nutritional status and relevant epigenetic signatures.

## Methods and analysis

### Study design and setting

The ENRICH study is a two-arm individually randomised open-labelled controlled trial nested within the AASH cohort study (figure 1).^25^ The study will be conducted in catchment areas of three primary health centres (PHCs) (Addagutta, Warasiguda and Sitaphalmandi) in Hyderabad, India which are within a vicinity of 5 km and have similar demographic and socioeconomic composition. These slums have a total population of ≈175 000 and previous studies in this area have found a high prevalence of childhood stunting (around 27% at 24 months age).^9^ It was also reported that the caloric intakes of children aged 18 months in this area were comparable to the National data of children aged 1–3 years with rural background. Women will be recruited in the study in the third trimester of pregnancy, and the egg intervention will start when the children are 9 months. Data and sample collection will be conducted as per the observational study protocol, including infant blood samples at 6 and 18 months; anthropometric measurements, dietary data and infant cognitive function at 9, 12 and 18 months of age. Blinding the participants is not possible due to the nature of the intervention, but the study staff measuring study outcomes will be blinded to the intervention group.^25^

**Figure 1 F1:**
[figure not shown]
CONSORT Flowchart of the study design

### Sample size

The sample size (70 in intervention and 280 in control group) was calculated with 90% power for an effect size of 0.32 in the length-for-age z score (LAZ) between the intervention and control groups with SD=0.70, drop-out of 10% and an allocation ratio of 1:4. This sample size is also adequate to detect 0.26 SD difference in LAZ between the two groups with 80% power and is also powered (80%) to detect a difference of 0.5 SD in the cognitive outcomes.

We believe that our study may result in a larger effect size (≥0.26 SD) than previous studies due to the intensively supervised nature of our intervention delivery which is likely to result in higher compliance to the supplement as compared with the previous studies. Our study intervention includes daily supply of ready to eat boiled egg in contrast to weekly delivery of raw eggs in Ecuador and Malawi studies,^11 12^ longer duration of intervention (9 months vs 6 months’ supply of eggs in previous studies), compliance targeted BCC including daily egg consumption record and an egg calendar. Recent studies on comprehensive supervised interventions have shown larger benefit (around 0.4 SD in LAZ) in improving linear growth faltering.^26^ Moreover, an intensively supervised intervention needs to have a larger effect size to be considered for potential scale-up.

### Outcome measures

The primary study outcome is the LAZ score at 18 months. The secondary outcomes include cognition measured by the Oxford Neurodevelopment Assessment (OX-NDA) at 12 months and the INTER-NDA (a multidimensional international assessment of child development) component of the INTERGROWTH- 21st NDA. These tests have been selected since these assessments are rapid (15 min), low cost and constructed specifically for use in low-income and middle-income country setting and can be administered by non-specialists in field sites for a large sample.^27^ It has strong agreement with the Bayley’s Scale for Infant Development-III (interclass correlation coefficients 0.75 to 0.88, p<0.001 for all domains.^28^ The OX-NDA showed moderate agreement for cognition and motor outcomes (ICCs 0.63 and 0.68, p < 0.001). The tests are designed to be free from cultural biases and the kit consists of common household items. The Home Observation for Measurement of the Environment (HOME) has been widely used to assess opportunities for cognitive stimulation at home setting.^29^ The scale consists of 45 items categorised into six subscales: receptivity, acceptance, organisation, learning materials, engagement and diversity. The researcher rates each item with a score of 1 if it occurred during the visit. Some items are also reported by the caregiver. Higher scores are indicative of a better environment. The scale has been previously used in India.^30 31^ The other secondary outcome measurements include plasma concentrations of insulin-like growth factor 1 (IGF-1), insulin-like growth factor binding protein-3 (IGFBP3), serum/plasma concentrations of essential amino acids, micronutrient status including; retinol, folate, vitamin B_12_, betaine, as well as red blood cell (RBC) fatty acids, DHA, choline and epigenetic (DNA methylation) signatures linked to the study outcomes. The detailed methodology has been described elsewhere.^25^

### Participant recruitment

The present trial is nested within the AASH observational cohort study where pregnant women (n=700) in the third trimester of pregnancy residing in the urban slums are being enrolled through the PHC after eligibility assessment and obtaining written informed consent. The data collection in pregnancy and during the follow-up of the offspring has been described elsewhere.^25^ Of these, 350 children born from February 2022 to March 2023 will be a part of the present trial; 70 children will be randomised to the intervention arm and 280 to the control arm. The control arm children will also be a part of the observational cohort.

### Eligibility

The inclusion criteria during pregnancy will be: healthy pregnant women in the age group 18–40 years, gestation 26–32 weeks, singleton pregnancy and willingness to comply with the study requirements. Children who were part of the AASH observational cohort and who attained 9 months at the inception of the ENRICH trial in November 2022 will be included. Out of these children, those who will relocate to a new area within next 9 months, those with a history of egg allergies (including family history), children with congenital anomalies or chronic morbidities, children whose parents were not willing to feed egg to their babies will be excluded from the study.

### Randomisation, intervention allocation and blinding

Each month, all children between 7.5 and 8.5 months of age will be randomly assigned to either the intervention or control group in a ratio of 1:4 after ascertaining the eligibility and obtaining written informed consent from the mother. Project staff collecting data on study outcomes will be blinded to the allocation sequence.^11^

Through a centralised block randomisation system, 350 children will be randomly allocated to blocks of 5 or 10 children, maintaining a ratio of 1:4 intervention and control children within each block. Allocation is concealed by sequentially numbered, opaque sealed envelopes.

### Trial intervention, intervention delivery and quality control

Egg supplementation will start on completion of 9 months of child age. The participant duration in the trial is for 9 months (till 18 months of age of the child). On week-days, one hen’s egg (medium-sized, weighing around 50 g, raw/boiled depending on the mother’s choice) will be delivered to children’s homes every day by project staff, and mothers will be asked to feed it to the child within 4 hours. On fifth day, extra raw eggs are supplied to cover for the weekend days. The mothers will be provided instructions on age-appropriate egg-based complementary food recipes through a purpose-made video during the first visit. The importance of feeding the egg to the index child and not sharing it with other family members will also be stressed during monthly counselling sessions to improve adherence to the intervention. This is a model of BCC developed based on evidence generated through best practices for Take-Home Rations of supplementary nutrition by Government of India.^32^ The specific messages were developed through formative research conducted with parents and grandmothers of young children. The project staff will observe the first feeding episode of complementary food containing eggs, and mothers will be counselled in case of minor gastric problems such as cramps in the stomach, nausea and vomiting.

Study staff will visit the households twice a week to observe the child feeding in the first month of the intervention and will encourage and support the mothers. Information on consumption of an egg by the child on the previous day is collected daily by the field staff while delivering the eggs in the intervention group. For comparison, data on eggs consumption will also be collected every month during a home visit in the control group children (online supplemental appendix 1).

10.1136/bmjpo-2023-001892.supp1Supplementary data

The eggs will be procured locally from a verified supplier. The quality control measures to ensure food safety of the intervention will include periodic assessment of the microbial contamination of eggs: both at the point of purchase and the point of use. Every month, random subsamples of eggs collected soon after purchase (three raw and three boiled eggs) and complementary food prepared using eggs for the child (from six households every month) will be analysed for microbial contamination (Salmonella, Shigella, total coliform count) at the NIN laboratory. Eggs will be randomly selected for assessing nutrient composition for major nutrients (energy, proteins, iron, folate, calcium, vitamin A, D, etc) every 3 months at the food chemistry laboratory of ICMR-NIN (Indian Council of Medical Research- National Institute of Nutrition).

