### Control group

The state government currently provides eggs (16 eggs per month for 7 months to 3 years) for beneficiaries of Integrated child development services (a government initiative for all women and children who can voluntarily enrol) as a part of the Rations. However, during formative research with mothers(n=100), it was found that children below 1 year of age are not fed whole eggs due to fear of indigestion and other reasons. Moreover, 59% of children were not fed eggs supplied through the government’s supplementary nutrition programmes due to intrahousehold sharing.^33^ Though there will not be any active intervention by the study team in the control group, all children from both the intervention and control groups may receive eggs as a part of Take-Home Ration, which may reduce the magnitude of the observed effect of the intervention. Also, there is a possibility of e ‘contamination’ of BCC messages in the control group in this individually randomised trial.

The number of eggs received through government programme and the number of eggs consumed by the child will be recorded for the intervention as well as control group. We will assess the mother’s knowledge of the nutritional benefits of eggs in both the groups at baseline and 18 months for comparison between the two groups (online supplemental appendix 1).

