### Data collection at baseline and during follow-up

Data collection in both the intervention and control groups would be done following the same protocol as the observational cohort. The parameters to be measured at different time points are listed in table 1. Details on the methodology for assessing primary and secondary outcomes are described elsewhere.^25^ A trained phlebotomist will draw a 3 mL venous blood sample at both 6 months and 18 months in children from the intervention group and a subsample of 70 children from the control groups. The methods for assessment of blood parameters and epigenetic signatures linked with stunting and cognition have been described elsewhere.^22 25^ Data on morbidity (including information on episodes of hospital admission and sick-child clinic visits) will be collected using a structured questionnaire every 2 weeks. Mothers will be encouraged to report any adverse events to the study staff. Data will be collected using the android interface of CommCare V.2.53 using Samsung A8 tab. The collected data will be securely stored in the database using encrypted codes. For data quality, we have used closed end questions wherever possible, and mandatory fields for core questions. Regex functionality is enabled for anthropometry data. The double data entries are manually managed at the supervisor level.

**Table 1 T1:** Variables measured at different time points

Measure	Timelines (intervention and control group)

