**Diet, anthropometry and cognition**	
Diet Multiple pass 24-hour diet recall with repeat in 10% of the sample Initiation of breast feeding Exclusive breast feeding and introduction to complementary foods	Dietary 24-hour recall at 6, 9, 12 and 18 months Breast feeding questionnaire at birth Breastfeeding questionnaire at 1–6 months
Anthropometry measurements Standing and sitting height, weight, skinfolds and MUAC Length, weight, head circumference, MUAC, knee-heel length and skinfolds	At third trimester of pregnancy and at 3, 6, 9, 12, 18 and 24 months at birth. Only weight only at 1, 2, 4 and 5 months.
Assessment of cognition with context-specific tests Home Observation Measurement of the Environment Oxford Neurodevelopment Assessment (OX-NDA) INTERGROWTH-21st Neurodevelopment assessment (INTER-NDA)	At 10–14 months and 18 months At 10–14 months At 22–24 months
Assessment of morbidity using structured pictorial charts	Completed by mother every day from birth until 18 months or every 2 weeks recall by the enumerator throughout the follow-up
Assessment of home environment	Using a structured questionnaire at 9 months

AAT, alpha-1-antitrypsin; AGP, alpha-1-acid gycoprotein; CRP, C reactive protein; IGF1, insulin like growth factor-1; IGFBP3, insulin-like growth factor binding protein 3; MPO, myeloperoxidase; MUAC, mid upper arm circumference.

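### Egg intake is recorded by different methods in the two arms; the between-arm intake contrast should come from the dietary recall that both arms share

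*Protocol article*

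**What the plan says.** The section on trial intervention, delivery and quality control sets one method per arm. For the egg arm: "Information on consumption of an egg by the child on the previous day is collected daily by the field staff while delivering the eggs". For controls: "For comparison, data on eggs consumption will also be collected every month during a home visit in the control group children". Deliveries are on weekdays, and "On fifth day, extra raw eggs are supplied to cover for the weekend days". The Sample size section counts the egg-arm record as part of the intervention, listing "compliance targeted BCC including daily egg consumption record and an egg calendar".

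The Control group section accepts that "all children from both the intervention and control groups may receive eggs as a part of Take-Home Ration" and that this may shrink the observed effect. It adds that "the number of eggs consumed by the child will be recorded for the intervention as well as control group", without naming the form or the interval. Supplemental appendix 1, cited in both sections, is not shown.

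Two other sources are common to the arms. The data collection section states: "Data collection in both the intervention and control groups would be done following the same protocol as the observational cohort". Table 1 then lists a multiple-pass dietary interview: "Dietary 24-hour recall at 6, 9, 12 and 18 months". It also lists red-cell fatty acids, amino acids, choline and betaine at 6 and 18 months in the egg arm and in 70 controls.

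**The concern.** A measure labelled as being for comparison should be taken the same way in both groups. Here the egg-arm mother answers the person who brings the egg, within a programme that counsels her each month to feed it to the index child and not share it. The control mother is asked once a month at a home visit. Interval, setting and the days covered all differ by arm, so a difference between the two records need not be a difference in eggs eaten.

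The plan needs this contrast. The government ration is 16 eggs a month, which is 16/30 = 53% of one egg a day. The formative finding that whole eggs are avoided applies to children under 1 year, and 18 − 12 = 6 of the 9 trial months fall after that age. If the effect on length-for-age is small or null, the reader must know whether the arms really ate different amounts. The additional per-protocol analysis could also be touched, if its population is defined from egg consumption.

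**Working it through.** The plan gives no figure for the intake contrast. Its one related figure is the sample size, so I checked that first and then the records.

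**1. Sample size.** Inputs from the Sample size section: difference 0.32, SD 0.70, power 90%, allocation 1:4, drop-out 10%. Two-sided alpha of 0.05 is my assumption. Intervention n = (1 + 1/4) × (1.960 + 1.282)² × 0.70² / 0.32² = 62.9, so 63, with 4 × 63 = 252 controls. Dividing by 0.9 gives 70 and 280, as stated. Egg intake does not enter this calculation.

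**2. Records side by side.**

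| | Egg arm | Control arm |
|---|---|---|
| Interval | each delivery day | monthly, about 9 contacts in 9 months |
| Period asked about | previous day | not given in the article |
| Asked by | staff delivering the egg | not given in the article |
| Tied to the intervention | yes, part of compliance counselling | no |

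**3. Day coverage in the egg arm.** With Monday to Friday deliveries, a previous-day question refers to Sunday to Thursday. That is 5 of 7 days, or 71%. Friday and Saturday are not asked about, unless the egg calendar is used to fill them; the article does not say so.

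**4. How far misreporting could move the contrast.** All inputs here are assumed: true intake 5.5 eggs a week in the egg arm and 1.5 in controls, so a true contrast of 4.0; over-reporting of 0 to 20% in the egg arm; error of −40% to +40% in controls. Apparent contrast = 5.5 × a − 1.5 × b:

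- a = 1.0, b = 0.6: 5.5 − 0.9 = 4.6
- a = 1.0, b = 1.4: 5.5 − 2.1 = 3.4
- a = 1.2, b = 0.6: 6.6 − 0.9 = 5.7
- a = 1.2, b = 1.4: 6.6 − 2.1 = 4.5

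The range is 3.4 to 5.7, or −15% to about +43%. The sign is not fixed.

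**5. What the shared recall can deliver.** Assume 63 and 252 children with two recalls each (12 and 18 months), 80% of egg-arm recall days with an egg, and 10% to 50% of control days. If the two days are independent, the SE of the difference is √(p(1−p)/(2×252) + 0.8×0.2/(2×63)): 0.038 at p = 0.1 and 0.042 at p = 0.5. The 95% half-width is then 7 to 8 percentage points. If a child's two days carried no more information than one, the SEs would be 0.054 and 0.059, and the half-width 11 to 12 points. That is usable for a contrast between arms, though not for classifying individual children.

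**The case against.** The strongest reply is that the plan already holds what is needed. The Control group section promises egg counts in both arms, possibly on one form in the appendix. The 24-hour recall is common to both arms, and biomarkers exist. The Statistical analysis section specifies no between-arm test of egg intake, and which source to tabulate is commonly left to the analysis plan. Much of this stands, and it is why the point is modest. It does not dispose of the point, because the article does assign a source to the comparison, and the only methods it describes for that purpose are the unequal ones.

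Several stronger readings are tempting and not supported:

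- A reader might infer that controls give month-long recall to someone with no part in the trial's promotion of eggs. The text gives monthly collection only; neither the recall window nor the visitor's role is stated.
- A reader might infer that the contrast is biased upwards. Control mothers could over-report ration eggs meant for the child, and step 4 shows that either sign is possible.
- A reader might put a figure on it. Suppose true intake is 24 eggs a month in the egg arm and 0.41 × 16 = 6.56 in controls, with 10% over-report and 30% under-report. The measured contrast is then 26.4 − 4.59 = 21.81 against 17.44, or 25% too large. The 24 and both error rates are chosen, and the 0.41 (100% minus the 59% not fed ration eggs) assumes that those children eat all 16. Even then, nobody would read 26.4 against 4.59 as similar intake.
- A reader might expect a shared instrument to be free of bias. Egg-arm mothers are unblinded and counselled, and can over-report to any interviewer. In step 4, over-reporting of 10% in that arm alone still gives 6.05 − 1.5 = 4.55 against 4.0.

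**Conclusion.** The point holds in a limited form. The article describes arm-specific collection of a quantity meant for comparison, and a contrast built from those two records is open to differential reporting and incomplete day coverage. The 5-in-7 coverage follows from the text if deliveries run on five weekdays and the question is asked literally. The direction and size of the reporting error are unknown; the 3.4 to 5.7 range only illustrates assumed inputs.

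The intention-to-treat comparison of length-for-age at 18 months does not use egg intake and is not threatened, and no sample-size change follows. The consequence is for interpretation, chiefly of a small or null effect given the contamination that the article itself acknowledges in its Control group and Significance and impact sections. This is an inexpensive improvement to the plan and does not affect its validity.

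**What to change.** State that the between-arm egg-intake contrast is taken from instruments identical in both arms:

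- The multiple-pass 24-hour recall at 12 and 18 months, with 9 months as baseline, is the main source.
- The egg-related biomarkers at 18 months, in the egg arm and the 70-control subsample, serve as support.
- If the monthly egg-consumption form is not already used in the egg arm, use it there too, with the same recall window and covering eggs from all sources.
- The daily delivery record is used only to describe adherence within the egg arm.

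The recall and biomarkers are already scheduled, so they cost nothing extra. The monthly form, if it has to be added, is a short questionnaire for 70 children. The price is precision: two on-treatment recall days per child, and biomarkers in only 70 of 280 controls with one post-baseline sample. Reporting bias from unblinded mothers is reduced but remains, and should be named as a limitation.
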